### Data processing and analysis

3.4

To increase the efficiency of clinical trials researchers embarking on prospective longitudinal studies will often include restrictive eligibility criteria to restrict potential mortality from existing comorbid conditions.^22^ Such restrictions in retrospective studies limit generalisability of the findings and result in significant loss of individuals included in the study. An alternative approach introduced by Charlson^22^ classifies patients with comorbid disease according to their risk of death from disease at entry to a study, allowing researchers to classify the risk of one‐year and 10‐year mortality.^22^, ^31^ Charlson Comorbidity Index (CCI) can be classified as mild (1–2), moderate (3–4) and severe (≥5).^25^ With each increased level of the comorbidity index, there is a stepwise increase in the cumulative mortality attributable to comorbid disease.^22^ CCI will be calculated from CPRD Aurum to predict a patient's 10‐year risk of mortality and managed as a confounding factor during multivariate analysis.

Not all aspects of health data are captured in CPRD, for example, socio‐economic demographics which are an independent effect modifier contributing to increased mortality in people with type 2 diabetes, with mortality risk increased in those in the most deprived neighbourhoods by as much as 11% per quintile of deprivation where the person also had a diabetic foot ulcer.^32^ Linkage to patient level indices of multiple deprivation (IMD) deciles will overcome this. IMD will be managed as a cofounding factor during multivariate analysis and this limitation will need to be addressed fully in our discussion.

We will use primary care demographic data and READ codes for CPRD Aurum and laboratory tests to confirm main potential confounders at baseline. These include age, sex, time since first use of diagnosis code (as a proxy for diabetes duration and age at diagnosis in years), multimorbidity (CCI), BMI, smoking status and laboratory results for HbA1c, systolic blood pressure (SBP) and total cholesterol. Ethnicity and patient level IMD will be included following linkages with relevant health datasets.

The CPRD dataset will be cleaned and checked for completeness prior to linkage with patient level indices of multiple deprivation (IMD), Hospital Episode Statistics (HES) Admitted Patient Care (APC) and Office for National Statistics (ONS) death registry datasets. Figure 1 demonstrates a visual representation of how data are stitched together and linked with other datasets.

**FIGURE 1 dom16257-fig-0001:**
[figure not shown]
Stitching of data and linkage of datasets.^35^, ^36^

Following data linkage to the HES APC dataset, ICD codes for 17 cause‐specific mutually exclusive admission clusters (Appendix 1) will be extracted as identified in a recent epidemiological analysis for people with diabetes in England^11^: ischaemic heart disease, stroke, acute myocardial infarction (MI), diabetes‐related cancers, non‐diabetes related cancers, hyperglycaemic crisis, major amputations, minor amputations, skin and bone infections, respiratory infections, kidney infections, sepsis, respiratory disease (non‐infectious, non‐cancerous), renal disease, chronic kidney disease, liver disease.

More than 50% of deaths in the United Kingdom do not occur in hospital, with ONS mortality data considered the gold standard for mortality records.^33^ Following data linkage with the ONS national death registry, cause‐specific mortality across 12 mutually exclusive clusters (Appendix 2) will be extracted as identified in a recent epidemiological study identifying causes of death in patients with diabetes in England^34^: ischaemic heart disease, stroke, other circulatory, other cancer, diabetes‐related cancer, dementia, diabetes, liver, renal, respiratory, other, injuries. In line with current reconciling guidelines date of death and cause of death will be taken from CPRD to enable linkage for the 25.11% of patients in England that are ineligible for linkage with ONS.^33^

The following recommendations will be applied when linking data from CPRD to ONS mortality data.^33^
If only CPRD date of death is present, this can be used as a reliable piece of information and has been previously validated.If only ONS mortality information is present, its date and causes of death can be used if the linkage rank is ≤2 (Table 2) and the date of death is within the linkage period being examined.If both CPRD and ONS dates of death are available, ONS will be used for the date of death and cause of death when the match rank is ≤2 and the date of death is within the linkage period being examined.If both CPRD and ONS are present and ONS date of death is outside the linkage period, or the match is ≥3 the CPRD date will be used to validate ONS. If the dates coincide ONS date of death and cause of death can be used. If not only CPRD date will be used.

**TABLE 2 dom16257-tbl-0002:** National Health Service (NHS) digital 8‐step linkage algorithm.^33^

Step	NHS number	Date of birth	Gender	Postcode
1	Exact	Exact	Exact	Exact
2	Exact	Exact	Exact	
3	Exact	Partial	Exact	Exact
4	Exact	Partial	Exact	
5	Exact			Exact
6		Exact	Exact	Exact
7		Exact	Exact	Exact
8	Exact			

### Study size

3.5

The study sample includes all patients in CPRD Aurum available during the study period who meet the inclusion criteria. A feasibility search on Aurum identified people meeting the study inclusion criteria (*n* = 605 710). A priori calculation of the sample size whilst presenting some uncertainty cannot be determined beforehand as the sample size will be reduced by inclusion of confounding variables and exclusion of some individuals.^19^ The sample size included in this study from feasibility counts is far larger than usually considered in hypothesis testing situations such as those proposed in this study. This gives us confidence we have sufficient sample size in this study for a reliable assessment of the research questions. Nevertheless, as an example, the 21 398 ‘*ever*’ patients and 584 312 ‘*never*’ patients identified would be sufficient to detect a difference in the proportion hospitalised (main outcomes) of approximately 1.9% with a power of 80% and a significance level of 5%.

### Statistical methods

3.6

Baseline characteristics of participants will be summarised using descriptive statistics (mean, median, interquartile range and standard deviations as appropriate). We will also summarise total number of hospital admissions and length of stay by age, age at time of diabetes diagnosis, diabetes duration, ethnicity and IMD decile.

The primary cohort is those who have ‘*ever*’ received DSME in each of the 10 years in the study to identify hospital admissions and cause of death during follow‐up. We will additionally have a matched diabetes cohort who have ‘*never’* received DSME to provide comparison (rate ratios).

An initial crude analysis will compare the proportion of hospitalisations and deaths between *ever* and *never* DSME groups. Chi‐squared tests will be used to compare these proportions. Similar tests will be used for subgroup analysis and alternative outcomes (cause‐specific hospitalisations and mortality).

Number of hospital admissions will be calculated to estimate relative risk of admissions and mortality by all‐cause and cause‐specific using a mixed Poisson model. Should the data be over dispersed a negative binomial mixed model will be adopted.

A Cox proportional‐hazards model will be used to measure time to event for first hospital admissions and mortality with the proportional hazards assumption checked using Kaplan—Meier curve plots and Schoenfeld residuals tests. If the proportional hazards assumption does not hold, then alternatives such as restricted mean survival times models will be used.

Baseline covariates will be reported among the ‘ever’ and ‘never’ groups, and a statistical test will be applied to see whether these differ significantly. These will be examined in multivariate models. We will address potential issues with confounding by indication firstly within the study design in which individuals in the ever group will be matched at baseline for age, sex, diabetes duration and age at diagnosis to individuals in the never group. All models will be adjusted a priori for CCI, IMD, HbA1c, BMI, smoking status, lipid level and SBP during multivariate analysis.

Statistical analysis will be conducted using R version 4.4.1. Alpha level will be set at 5% for statistical significance.

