### Study design

3.1

This 10‐year retrospective open cohort study^19^ will include adults over the age of 18 years^†^, 12 months from the first use of a clinically recorded diagnosis of type 2 diabetes or type 2 diabetes‐related encounter registered to an English GP practice between 29 March 2011 and 29 March 2021^‡^. Patients will be identified from the CPRD database using READ codes to run analyses of the agreed set of exposures and outcomes.

^†^Patients who turn 18 during the study period will be included from the point of turning 18.

‡At the time of CPRD approval for this protocol data linkage to Hospital Episode Statistics (HES) Admitted Patient Care (APC) data were restricted up to and including 29 March 2021.

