### Data selection

3.3

To minimise the impact of incorrect information or flawed subject selection the ‘*ever’* cohort will be matched at baseline to patients who have ‘*never’* received DSME (*n* = 584 312). Age,^22^, ^23^ age at diagnosis and diabetes duration^22^, ^24^, ^25^, ^26^ are the most important predictors of one‐year mortality in type 2 diabetes.^27^ Every decade of earlier diabetes diagnosis is associated with 3–4 years of lower life expectancy.^24^

Cohort analysis, systematic review and meta‐analysis have considered the association between diabetes and sex, demonstrating that women generally have a higher risk of coronary heart disease and all‐cause mortality (58%) compared to men and a 13%–17% greater risk of all‐cause mortality.^28^, ^29^ Moreover, the additional likelihood of developing cancer and the higher risk of premature mortality from having diabetes is more pronounced in women.^30^

Patients will therefore be matched at baseline for age ± 5 years, age at diagnosis ±5 years, diabetes duration ±1 year and sex who are present in the dataset from the same start year or earlier.

This study will adopt an intention‐to‐treat analysis, with patients contributing only to the original exposure group in which they have been assigned, irrespective of when they receive DSME. Baseline for the ‘ever’ group and their matched controls will be the date of DSME intervention. Patients will remain exposed until they are censored by death, leave the GP practice, leave a GP practice which contributes to CPRD data or end of the study period (29 March 2021).

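### Chi-squared tests on crude proportions are the only method named for subgroups, and for cause-specific outcomes they stand beside an adjusted model with no stated precedence

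*Protocol article*

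**What the plan says.** Section 3.6 (Statistical methods) begins the comparison with a crude step: "An initial crude analysis will compare the proportion of hospitalisations and deaths between" the two exposure groups, for which chi-"squared tests will be used to compare these proportions". The paragraph closes by extending the method: "Similar tests will be used for subgroup analysis and alternative outcomes", with cause-specific hospitalisations and mortality given in brackets as the alternative outcomes.

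The same section then plans regression models:

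- A mixed Poisson model, or negative binomial if over-dispersed: "Number of hospital admissions will be calculated to estimate relative risk of admissions and mortality by all"-cause and cause-specific grouping.
- A Cox proportional-"hazards model will be used to measure time to event for first hospital admissions and mortality".
- Adjustment: "All models will be adjusted a priori for CCI, IMD, HbA1c, BMI, smoking status, lipid level and SBP during multivariate analysis".

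Neither model sentence mentions subgroups.

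On design, section 3.1 describes a 10-"year retrospective open cohort study". Section 3.3 (Data selection) starts follow-up at the DSME date, which matched controls share, and ends it individually: "Patients will remain exposed until they are censored by death, leave the GP practice", the practice ceases to contribute, or the study closes on 29 March 2021.

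**The concern.** There are three separate difficulties with the subgroup method as written.

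1. **Person-time.** The proportion ever admitted, or dead, depends on how long people were observed, and the chi-squared test does not use that time. If one group leaves or dies sooner, its proportion admitted falls even when its admission rate is the same. Depending on which group is lost faster, this can create, hide or reverse a difference.
2. **Confounding.** The plan treats CCI, IMD, HbA1c, BMI, smoking, lipids and blood pressure as confounders serious enough to adjust for in every model. The only test it names for subgroups adjusts for none of them.
3. **Effect modification.** A test in each subgroup asks whether there is an association in that subgroup. It does not ask whether the association differs between subgroups, and a significant result in one stratum beside a non-significant result in another does not show that it does.

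For cause-specific outcomes the problem is narrower. A crude test and an adjusted model are both planned, alpha is 5% with no exemption for the crude tests, and nothing says which one is to be interpreted if they disagree.

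**Working it through.** The plan gives no figure on this point. It also gives no event or loss rates, so the rates below are assumptions. The calculation asks how often a chi-squared test at 5% rejects when the two groups have the **same** hazard.

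**Inputs**

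- Group size n = 21 398, the ever count in section 3.5. Equal groups (1:1) are assumed, because the matching ratio is not stated. A subgroup of about one tenth is taken as 2 140 per group.
- Index dates uniform over the 10 years and shared within matched sets, so administrative follow-up T is uniform on 0 to 10 years in both groups.
- Event hazard λ = 0.10 per year in both groups (assumed). λ = 0.01 per year serves as a cause-specific level (assumed).
- Exponential loss at rate c: 5% per year in the ever group; 5%, 6% or 7% per year in the never group (assumed).

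**Expected crude proportion.** With k = λ + c, averaging over T gives

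P = (λ/k) × [1 − (1 − e^(−10k))/(10k)].

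- c = 0.05: k = 0.15, P = 0.6667 × (1 − 0.7769/1.5) = 32.14%.
- c = 0.06: k = 0.16, P = 0.625 × (1 − 0.7981/1.6) = 31.32%.
- c = 0.07: k = 0.17, P = 0.5882 × (1 − 0.8173/1.7) = 30.54%.

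Mean potential follow-up (to loss or study end) is (1/c) × [1 − (1 − e^(−10c))/(10c)], which gives 4.26, 4.13 and 4.01 years.

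**Rejection rate.** With d the difference in proportions, p̄ their mean, s0 = √(2p̄(1 − p̄)/n) and s1 = √((p1(1 − p1) + p2(1 − p2))/n):

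rejection = Φ((d − 1.96 s0)/s1) + Φ((−d − 1.96 s0)/s1).

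For 5% versus 7% loss and n = 21 398: d = 0.01597 and s0 ≈ s1 ≈ 0.00448. The first term is Φ((0.01597 − 0.00879)/0.00448) = Φ(1.60) = 0.945, and the second is negligible.

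| Loss per year, ever vs never | λ = 0.10, n = 21 398 | λ = 0.10, n = 2 140 | λ = 0.01, n = 21 398 |
|---|---|---|---|
| 5% vs 5% | 5% | 5% | 5% |
| 5% vs 6% | 44% | 9% | 10% |
| 5% vs 7% | 95% | 20% | 24% |

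**Check by simulation** (1000 runs per setting). For 5% versus 7% loss, chi-squared rejected in 96.0%, 20.5% and 23.8% of runs in the three columns. A test of events per person-year on the same data rejected in 5.4%, 4.0% and 6.2%.

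The false difference therefore comes from ignoring person-time. It is absent when loss is equal and grows quickly once loss differs by one or two points a year. In this example the never group is lost faster, so its crude proportion is too low and attenders look worse than they are. If the ever group were lost faster, the sign would reverse.

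The confounding and interaction points need no arithmetic. They follow from setting the subgroup sentence beside the model sentences in section 3.6.

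**The case against.** **The chi-squared step is labelled initial and crude.** An unadjusted first table before regression is routine, and the subgroup sentence sits in that paragraph. This stands to the extent that the crude tables may stay. But for the overall and cause-specific comparisons a model follows, whereas for subgroups none is named, and nothing marks the subgroup p-values as descriptive.

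**Cause-specific outcomes are already modelled.** This stands. A reader might infer from the closing sentence of the paragraph that conclusions on cause-specific outcomes rest on chi-squared alone. They do not, because the next paragraph plans a Poisson or negative binomial model for them and all models are adjusted. Only the order of precedence is open.

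**Individually varying follow-up is not enough.** This also stands. A reader might infer that an open cohort with follow-up of anything up to 10 years makes the crude test misleading by itself. It does not: matched controls share the index date and the administrative end, so a false difference needs loss or death to differ between the groups. The documents do not show that it does. There are reasons to expect it: the study's own hypothesis is that DSME affects mortality, and people who die or leave early have less time to acquire a DSME code. Neither reason supplies a rate.

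**Ignoring the matching.** With positive correlation within matched sets this normally makes the crude test conservative. It is a reason to analyse the data properly, not a source of the false positives above.

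**The 1.9% in section 3.5.** It is tempting to set the artefact against this figure as the difference the study was sized to detect. The article offers it only as an example and says the sample is all eligible patients, so it is no yardstick here.

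**Subgroup detail may be in an unseen SAP.** It may, and the lack of a list of interactions is not criticised. The point is that the article does state a subgroup method, and that method is unsuitable for inference.

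**Conclusion.** The point holds for subgroups and, in a weaker form, for cause-specific outcomes. For subgroups, the only method named uses neither person-time nor the plan's own confounders and cannot test effect modification. That conclusion rests on the text alone. For cause-specific outcomes, an adequate adjusted model is planned and the defect is the missing rule of precedence.

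The numerical size is conditional on the assumed hazards, 1:1 groups, exponential loss and, above all, a between-group difference in loss or death. It runs from no inflation with equal loss to near-certain false rejection in the full cohort with a gap of two points a year. In smaller subgroups or for rarer outcomes the inflation is more modest. This should be corrected before analysis, but it does not undermine the main all-cause analyses, for which adjusted models are already specified.

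**What to change.** Amend section 3.6, or the SAP, to say that:

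- Chi-squared comparisons of crude proportions are descriptive only, overall, in subgroups and for cause-specific outcomes.
- Subgroup inference uses the planned adjusted Cox and Poisson or negative binomial models, with person-time accounted for (for example a log person-time offset in the count models), the matching respected, and a DSME-by-subgroup interaction term as the test of effect modification.
- For cause-specific outcomes the adjusted models take precedence over the crude tests.

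Reporting person-years and reasons for censoring by exposure group beside the crude proportions would show whether loss does differ.

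The models are already planned, so the cost is a change of wording and slightly more analysis. The interaction terms will have wider intervals than the within-subgroup estimates, and some subgroup questions may remain unresolved.

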### Limitations, generalisability and interpretation

4.1

The medical data available in CPRD are collected during clinical consultations rather than for research, thus the data may be limited by recording quality, and there may be variation in the consistency and accuracy of reporting and coding by GPs. This may introduce inaccuracy into the study findings.

Although CPRD data on diabetes diagnosis has a high level of completeness, not all patient groups or GP practices are captured, for example, private patients, prisoners or some residential home patients. Moreover, some patients chose to opt out of CPRD, and some are exception‐reported by GPs. Furthermore, CPRD data capture may be less complete for ethnicity and socio‐economic demographic data, but this can be largely overcome by data linkage.

This study is observational by nature and reverse causality cannot be excluded as a possible explanation for associations or inferences. We are reliant on the accuracy of ICD‐10 codes and SNOMED‐CT codes to define outcomes. These limitations may introduce bias to the study and will be fully acknowledged in the discussion. Although we will match groups at baseline and manage confounding a priori, potential residual confounding can never be completely eliminated, and causality would need to be confirmed in a randomised controlled trial.

This study has the potential to benefit patients by informing guidelines and clinical strategies for people living with type 2 diabetes.

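### DSME exposure rests on GP-entered codes, yet GP practice is in neither the matching nor the adjustment set and is not named in the Cox model, so between-practice confounding is left open and standard errors may be somewhat too small

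*Protocol article*

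**What the plan says.** All references are to the protocol article.

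- **Exposure (3.2 Sample, Table 1).** A patient is 'ever' exposed if one of the listed DSME codes is in the GP record.
- **Matching (3.3 Data selection).** "Patients will therefore be matched at baseline for age", and also for age at diagnosis, diabetes duration and sex, with a condition on start year. GP practice is not a factor. The number of controls per exposed patient is not given.
- **Models (3.6 Statistical methods).** Crude proportions are compared by chi-squared tests. Admission counts are analysed "using a mixed Poisson model", or with a negative binomial mixed model if overdispersed; the random effect is not named. For first admission and death, a Cox "model will be used to measure time to event for first hospital admissions and mortality". No stratum, frailty or clustered variance is named for it.
- **Adjustment (3.6).** The list for all models is CCI, IMD, HbA1c, BMI, smoking, lipids and SBP. Practice is not on it.
- **Limitations (4.1).** "there may be variation in the consistency and accuracy of reporting and coding by GPs". Residual confounding is conceded in general terms.

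**The concern.** If the recording of DSME depends partly on the practice, 'ever' status depends partly on where a patient is registered. A recorded attender from a practice that codes thoroughly can then be matched with a 'never' patient from a practice that does not. If thorough coding goes along with other features of care that affect admission or death, the hazard ratio for DSME absorbs them. Patient covariates and IMD do not measure how a practice works, and a larger sample does not remove this bias.

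The second effect is on precision. Where exposure and outcome both cluster by practice, standard errors that ignore practice are too small and a nominal 5% test rejects too often.

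**Working it through.** **1. Is practice controlled anywhere in the stated lists?**

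| Element | What is listed | GP practice? |
|---|---|---|
| Matching (3.3) | age, age at diagnosis, duration, sex, start year | no |
| Adjustment, all models (3.6) | CCI, IMD, HbA1c, BMI, smoking, lipids, SBP | no |
| Cox model (3.6) | no practice term named | not named |
| Count model (3.6) | mixed model, random effect unnamed | possible, not stated |
| Chi-squared tests (3.6) | independent-observation test | no |

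The first two rows are explicit lists, so the confounding part of this point does not rest on silence alone. The Cox row is silence.

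**2. Does the plan's own precision figure allow for clustering?** Section 3.5 takes 21,398 'ever' and 584,312 'never' patients and says they suffice for "a difference in the proportion hospitalised (main outcomes) of approximately 1.9"%, "with a power of 80% and a significance level of 5"%. No baseline proportion is given. A two-sided test is assumed here, and the formula at a 50% baseline, which gives the largest detectable difference, is

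(1.96 + 0.84) × √[0.25 × (1/21,398 + 1/584,312)] = 0.0097, or about 0.98 percentage points.

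The stated 1.9 is not reproduced as a difference in proportions. Without the factor 0.25 the same expression gives 0.0195, which is Cohen's h, so the figure looks like an arcsine effect size read as a percentage. Reading it as a clustering allowance would need a design effect of about 3.8 even at a 50% baseline, and none is mentioned. Section 3.5 therefore gives no sign that practice was considered.

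**3. How large could the effect on standard errors be?** For an exposure that varies within practices, the approximate variance inflation is

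DE = 1 + (m − 1) × ICC(outcome) × ICC(exposure),

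where m is the number of analysed patients per practice. The standard error grows by √DE, and the actual error rate of a nominal 5% test is 2 × [1 − Φ(1.96/√DE)].

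Input from the document: 21,398 'ever' patients (3.5). Assumptions, none of them in the document: 1,000 to 1,500 practices, outcome ICC 0.01 to 0.02, exposure ICC 0.1 to 0.3, and a matching ratio of 1:1 (2 × 21,398 = 42,796 patients) or 1:4 (5 × 21,398 = 106,990).

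| Matching | Case | m | DE | SE factor | Actual error of 5% test |
|---|---|---|---|---|---|
| 1:1 | low: 1,500 practices, 0.01, 0.1 | 28.5 | 1 + 27.5 × 0.001 = 1.03 | 1.01 | 5.3% |
| 1:1 | high: 1,000 practices, 0.02, 0.3 | 42.8 | 1 + 41.8 × 0.006 = 1.25 | 1.12 | 8.0% |
| 1:4 | low | 71.3 | 1 + 70.3 × 0.001 = 1.07 | 1.03 | 5.8% |
| 1:4 | high | 107.0 | 1 + 106.0 × 0.006 = 1.64 | 1.28 | 12.5% |
| either | exposure ICC = 0 | any | 1.00 | 1.00 | 5.0% |

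The high rows need every assumption at its upper end. The last row shows that without clustering of exposure there is no inflation.

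**4. How large could the confounding be?** The document gives nothing from which to size it, and no figure is offered.

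**The case against.** The strongest reply is that this is a condensed article. Robust variance or a frailty term is detail that a fuller plan could supply, and the mixed count model may already have practice as its random effect. That stands for the variance part: the article does not state that Cox observations are treated as independent. It does not answer the confounding part, because the matching and adjustment sets are written out and practice is in neither.

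Several stronger readings are tempting but are not supported:

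- **That the intervals are too narrow.** A reader might infer this from the missing practice term. DSME is an individual-level exposure, so inflation depends on the product of two ICCs that the document does not give, and it can be negligible. The planned covariates could also reduce practice-level variation in outcome.
- **That DSME referral, or admission and death rates, differ by practice.** The document does not say so. Section 4.1 says only that coding and reporting may vary by GP.
- **That the error rate is grossly inflated.** Applying the same formula to all 605,710 patients gives much larger values, but the planned comparator is a matched group.
- **That the chi-squared tests carry the main inference.** Section 3.6 presents them as an initial crude step, with similar tests for subgroups and cause-specific outcomes. The adjusted results come from the models.

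It is also fair to say that section 4.1 already concedes residual confounding. That is a general caveat, and section 3.6 plans no analysis that would show whether this particular source matters.

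**Conclusion.** The point holds as a risk that is cheap to address. Exposure is defined by GP-entered codes whose consistency the protocol says may vary, and the listed matching and adjustment sets give no control for practice. Between-practice confounding is therefore open, with unknown size and direction. The effect on precision is secondary: standard errors about 1 to 12% larger with 1:1 matching and 3 to 28% larger with 1:4, resting wholly on the assumed number of practices, ICCs and matching ratio, and falling to nothing if exposure does not cluster.

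**What to change.** In section 3.6:

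1. Use variance clustered on the practice identifier in the Cox models.
2. Name practice as a random intercept in the Poisson or negative binomial mixed model.
3. Add, as a sensitivity analysis, a Cox model with the baseline hazard stratified by practice.

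The third item is the check on confounding. Clustered variance leaves the hazard ratio unchanged, and a shared frailty assumes that the practice effect is independent of exposure, so neither removes confounding by practice. The stratified model compares 'ever' and 'never' patients within the same practice. A clear difference between its hazard ratio and the main one would suggest that practice matters, allowing for its lower precision.

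The matching factors can stay as they are. The cost is a sentence or two of plan wording, somewhat wider intervals and, in the stratified model, loss of information from practices without both 'ever' and 'never' patients. The practice registration data should be to hand, since the censoring rule in section 3.3 already depends on patients leaving a practice.
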